#### Plans to Provide Access to the Full Protocol, Participant-Level Data, and Statistical Code

The full protocol will be published open access, and anonymized participant-level data sets and statistical codes will be shared publicly through a permanent weblink that will be provided by the publishing journal. Since the primary country of recruitment, which approved and registered the study prior to recruitment, lacks a publicly available electronic research register, this protocol has been retrospectively registered with the WHO-approved Pan African Clinical Trials Registry (PACTR202308851460352).

### Oversight and Monitoring

#### Composition of the Coordinating Center and Trial Steering Committee

The principal investigator and a central study administrator will form a steering committee that will run the day-to-day activities of the trial. The trial will have 2 onsite overseers and 2 off-site supervisors. In addition, the principal investigator will provide organizational support to rural trauma teams at the intervention study centers through weekly audit meetings. Each of the rural trauma teams is composed of a road traffic law enforcement professional, a third-year medical student, a fifth-year medical student, an intern doctor or nurse, and a specialty surgery resident.

#### Composition of the Data Monitoring Committee, and Its Role and Reporting Structure

The research and ethics committee of Mbarara University of Science and Technology is the designated independent data monitoring committee that will oversee this trial (reference number: MUREC 1/7; 05/5-19). The committee reports directly to the Uganda National Council for Science and Technology. The council, at its discretion, can recommend continuation, amendments, or termination of the trial at any time.

### Adverse Event Reporting and Harms

Immediate medical concerns from participants will be reported to their attending clinicians. Any reported adverse events and other unintended effects of trial interventions or trial conduct will be reported to the trial monitoring committee. Patient-reported adverse outcomes resulting from the intervention (study) rather than biological injury progression will be captured during the follow-up interviews and evaluated on a 5-point Likert scale in accordance with the framework described by Okoniewska et al [48] as follows: (1) no evidence that the event is due to the intervention, (2) little evidence that the event is due to the intervention, (3) the event is possibly due to the intervention but most likely due to injury, (4) the event is more likely due to the intervention than injury, and (5) the event is definitely due to the intervention. Case files with 4 to 5 points will be forwarded for external auditing in surgery departmental meetings to ascertain if the adverse event was preventable, ameliorable, or neither.

### Frequency and Plans for Auditing Trial Conduct

The trial monitoring committees will independently conduct annual and impromptu audits and may choose to extend or terminate the trial at any time. Such situations that could warranty termination include adverse events directly attributable to the intervention. The investigators will submit annual progress reports to the committees each year as part of continuing review.

### Plans for Communicating Important Protocol Amendments to Relevant Parties

Any protocol amendments will be submitted to the data monitoring committee. Any approved amendments will be communicated to the Uganda National Council for Science and Technology and trial participants, and will be updated in the registries within 5 working days following approval.

### Ancillary Studies

This trial has been approved with 2 ancillary studies. The first is a study to assess the effect of the RTTDC on provider knowledge, and the second is a qualitative study to assess the barriers to injury care as perceived by traffic police, medical trainee frontline workers, and individuals encountered in the real-time management of patient participants. The data collection team for the qualitative study will be surgery residents at the 6 regional referral hospitals who will be blinded to the cluster or treatment allocation. The results of the ancillary studies will be collected and analyzed separately and will be concealed from the trial team until the analysis of the main clinical trial findings is nearly complete. We hope that the findings of the ancillary studies will complement and inform the interpretation of the trial findings.

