### Study Setting

This study will be conducted in 6 specialized teaching and regional referral hospitals in Uganda, including Kiryandongo, Jinja, Hoima, Fort Portal, Mubende, and Kampala International University Hospital. These facilities have similar characteristics and serve as teaching, residency, and internship sites for undergraduate and graduate medical doctors and nurses. The hospitals offer 24/7 emergency surgical services for trauma patients through multidisciplinary teams of orthopedic, general, and visiting neurosurgeons, as well as imaging, rehabilitation, and physiotherapy. Each surgical department in these facilities is typically composed of about 1-4 faculty members, 2-4 specialty residents often referred to as senior house officers, 4-6 interns, and 10-30 undergraduate medical trainees.

These facilities are suited for this study as they serve both rural populations and populations in newly created populous cities that are still struggling with urban planning. Uganda is the 8th most populous country in Africa and the 30th most populous country in the world [9], and its trauma surveillance systems are in the infancy stage with weak preaccident and postaccident responses [6,12]. Despite efforts made in the past decade by the Ugandan government to address the unmet need for trauma care through infrastructure development, such as equipping operating theaters and intensive care units (ICUs) in public hospitals, limited standardized preservice and in-service trauma training, prehospital delays, and human resource constraints still contribute to preventable trauma mortalities [14]. To guarantee the quality of data for this project, a prospective motorcycle trauma outcome registry (MOTOR) will be piloted at the participating 6 regional referral hospitals in parallel with this trial.

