#### Collection of Informed Consent

All participants or their legally authorized representatives (for minors and unconscious patients) will endorse a predesignated consent form document with their signatures in the presence of the principal investigator or research assistants (surgery specialty residents).

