### Interventions

#### Explanation for the Choice of Comparators

The intervention for this trial is based on the fourth edition of the RTTDC of the American College of Surgeons [20], which will be delivered to medical trainees, interns, and traffic law enforcement professionals at the 3 intervention study centers (intervention group). Specialty surgical residents will be trained as faculty who will later serve as trainers since they directly supervise interns and undergraduate medical students in Ugandan settings. The research and ethics committees approved training residents as opposed to specialists to avoid constraining the scarce specialized human resource as this is a trainee-capacity building trauma education program. Moreover, consultants rarely attend to trauma patients for immediate resuscitation as the first point of contact in Ugandan settings. The patient participants at intervention sites will be those with motorcycle accident–related injuries at any of the study sites. The comparator in this trial is a control group of hospitals that will offer standard care to eligible patients, without their care providers receiving the RTTDC training intervention.

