#### Intervention Description

The 2-day RTTDC interventional training will be conducted in designated spacious multimedia surgical simulation conference rooms at the study sites randomized to the intervention arm and will be delivered in the described standard format [20]. This training model is the most appropriate for Uganda, with its health worker to patient ratio of 1:25,000 and its large population of 48 million [12]. The model dwells on team concepts to improve coordination and efficiency of the existing “skeletal” health structure in the rural environment. We hope to train a total of 66 road traffic police officers, 12 specialty residents, 30 intern doctors, 140 fifth-year medical students, and 264 third-year medical students. These figures have been determined based on the average annual number of traffic police officers and trainees at the respective regional police headquarters and hospitals [25].

Our target is to train at least 80% of each cohort of eligible trainees identified every 1-5 months within the surgery department during the 4-year study period until the required trainee and patient participant sample sizes are attained. If trainees drop out prior to completion of data collection, compensations will be made to maintain the criterion during the next cohort of surgical rotation trainee intake. The details of how the training will be conducted have been provided elsewhere [25]. The research core team has agreed that trainee participants who score more than 60% in posttraining trauma-based multiple-choice questions (MCQs) at the intervention sites will be retained to form a rural trauma team network, which will constitute multiple local 6-member trauma committees of first responders with defined roles (ie, each team having 5 medical trainees and 1 contact road traffic officer).

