To enable an active “alarm” activation criterion for the trauma committees, closed-loop communication, and a smooth “handover” process from police officers to medical trainees prior to patient transfer, the trained traffic officers on highways will serve as focal contact persons for the rural trauma teams from the parish (subcounty) level. In the event of a road traffic accident, teammates will freely contact each other both within and across teams to coordinate evacuation, consultation, referral, and arrival at recipient centers, with the support of trained interns and surgery residents as team leaders. Weekly audit meetings will be conducted remotely via Zoom (Zoom Video Communications) to discuss team challenges, otherwise a trained surgery resident will be available 24/7 to advise on referrals, transfers, and treatments in liaison with consultants who may be physically or remotely available. The control hospitals in this trial will be allowed to provide routine standard care without the RTTDC intervention as summarized in Figure 1.

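### The barriers study calls its resident data collectors blinded to allocation, but residents at the three intervention hospitals teach the course and lead the trauma teams, so the claim cannot hold once training starts

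*Protocol article*

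**What the plan says.** Under Ancillary Studies, the protocol article describes a qualitative study of barriers to injury care as seen by traffic police, trainee frontline workers and people met in the course of managing patients. Its data collectors are "surgery residents at the 6 regional referral hospitals who will be blinded to the cluster or treatment allocation". The results are to be kept from the trial team until the main analysis is nearly done, and then used to help interpret the trial.

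Elsewhere the article gives surgery residents a part in delivering the intervention:

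- Explanation for the Choice of Comparators: "Specialty surgical residents will be trained as faculty who will later serve as trainers".
- Intervention Description: teammates coordinate care "with the support of trained interns and surgery residents as team leaders", and "a trained surgery resident will be available 24/7 to advise on referrals, transfers, and treatments".
- Composition of the Coordinating Center and Trial Steering Committee: each rural trauma team includes "a fifth-year medical student, an intern doctor or nurse, and a specialty surgery resident".
- Intervention Description, on numbers to be trained: "66 road traffic police officers, 12 specialty residents, 30 intern doctors".
- Study Setting, on the make-up of each surgical department: "2-4 specialty residents often referred to as senior house officers".

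The course is held on site, at hospitals randomized to the intervention only. Control hospitals give standard care without it.

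**The concern.** Someone who teaches a course held only at intervention hospitals knows that hospital's allocation. The blinding statement is therefore at odds with the residents' assigned roles, unless each intervention hospital has residents who stand outside the course and remain unaware of it.

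Two things are at stake. First, readers would take the barriers data as blinded when they are not. Second, the collector's position differs by arm. At an intervention hospital, a resident asks trainees and police officers about barriers after residents there have taught them and led their teams. At a control hospital, no resident has a course role. Answers about teamwork, communication and referral could depend on who is asking. Barriers are a tertiary outcome (Outcomes), but both Ancillary Studies and Study Limitations say the ancillary findings will inform how the trial is read.

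**Working it through.** The plan gives no figure for the number of collectors, so there is none to reproduce. The check has three parts.

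**1. Is there a pool of uninvolved residents?**

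Inputs:
- 3 intervention hospitals (Explanation for the Choice of Comparators)
- 2 to 4 residents per surgical department (Study Setting)
- 12 residents to be trained, and a target of at least 80% of each eligible cohort in the surgery department (Intervention Description)
- Assumption: one surgical department per hospital

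Calculation:
- Residents in post at one time: 3 × 2 = 6 to 3 × 4 = 12.
- Residents to be trained per intervention hospital: 12 / 3 = 4, the top of the stated range.
- The training number therefore equals or exceeds the residents in post at any one time.
- If the 80% target is applied to residents within a department: 0.8 × 2 = 1.6, 0.8 × 3 = 2.4 and 0.8 × 4 = 3.2. Rounded up, these are 2 of 2, 3 of 3 and 4 of 4. At these headcounts the target means every resident.
- If the target is pooled over residents at the three hospitals: 0.8 × 6 = 4.8, so 5 of 6; 0.8 × 12 = 9.6, so 10 of 12. One or two residents could remain untrained.

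Two things could loosen this. Residents turn over during the four-year study period, so 12 may be a smaller share of all who ever rotate. The 80% may also apply to trainees of all grades together, which would allow more untrained residents. Even so, an untrained resident in a department of 2 to 4 works beside the course, the trauma teams and the round-the-clock resident adviser. Being untrained does not make that resident unaware of the hospital's allocation.

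**2. Could a masking device help?**

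The section on who will be blinded describes allocation codes, and only for patients and outcome assessors. Codes cannot hide an on-site course from the people who teach it or work beside it.

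**3. When are the barriers data collected?**

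- Patient and Public Involvement places a one-day meeting on barriers at each site in the month before the study begins. Participant Timeline puts randomization 3 weeks before training. If study start and training start coincide, roughly the first week of that month precedes randomization, and all of it precedes the course. Blinding may hold for these meetings.
- Participant Timeline also has individual barriers documented throughout the study period, and Ancillary Studies refers to people met during real-time patient care. At intervention hospitals these data come after training starts, and blinding cannot hold for them.

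**The case against.** The strongest reply is that this is a single phrase about a tertiary, qualitative study whose own protocol is published elsewhere and is not at hand. Methods for Additional Analyses plans only content analysis of themes presented as percentages, with no test between arms. Nothing says the same individuals both train and collect. This limits the consequence, and it stands. It does not rescue the statement, because the claim fails for any resident working in an intervention department, whether or not that person teaches.

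Four stronger readings are tempting but not supported:

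- **All collectors at intervention hospitals are trainers.** The article gives neither the number nor the identity of the collectors.
- **The bias favors the course.** Respondents might hold back team problems from their own trainer. Teams that review their difficulties in weekly audit meetings might equally report more of them. Some respondents, such as caregivers, are not among those the residents teach or lead. The documents fix neither direction nor size.
- **Concealment from the trial team also fails, because residents act as research assistants who witness consent.** What is concealed is the results of the ancillary studies. A resident who holds some raw responses does not reveal collated results.
- **The main trial outcomes are compromised.** Medical officers collect those outcomes, not residents. Whether the officers are truly blinded is a separate question.

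**Conclusion.** The concern holds for barriers data collected at intervention hospitals after training starts: the stated blinding is a property the design cannot have. It may hold for the consultative meetings before the study. The conclusion rests mainly on the residents' roles as trainers, team leaders, team members and advisers. The count of 12 to be trained against 6 to 12 in post supports it, assuming one surgical department per hospital.

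A difference in the collector's relation to trainee and police respondents follows by arm. Its effect on the barrier percentages cannot be quantified from the article. The matter is worth correcting because the findings are meant to inform interpretation, but it is confined to a tertiary outcome and leaves the primary and secondary outcomes untouched.

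**What to change.** In Ancillary Studies:

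1. Withdraw the blinding claim for barriers data collected during the trial. If it is kept for the pre-study meetings, say so and give their dates relative to randomization.
2. Record and report, by site, whether each collector was an RTTDC trainer or team member, or neither.
3. Report the barriers data as unblinded.
4. State that a difference in barrier percentages between arms will not be interpreted as an effect of the intervention.

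Keep the concealment of ancillary results from the trial team, which is a useful safeguard. Do not pass collection to the project medical officers. They are the designated blinded assessors for the primary and secondary outcomes, and interviewing trained teams about barriers would expose allocation to them.

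The cost is a change of wording, one descriptive item per collector and a sentence of limitation. Last follow-up was on August 27, 2023, so collection is probably complete; all four steps can still be taken at the reporting stage, provided the collectors' roles can be recovered from site records.

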### Dissemination Plans

Participants of the RTTDC training will receive feedback after the posttest questionnaire evaluation. Patient participants will be advised on the next plans of management during follow-up calls or through outpatient consultations. Before presentation of the study findings at scientific conferences and publication in peer-reviewed journals, copies of the findings in final bound reports will be submitted to the main libraries of the participating hospitals, the departments of surgery, and the internal review boards of Mbarara University of Science and Technology, Kampala International University, and Uganda National Council for Science and Technology.

The implications of the findings will be shared with authorities, including intern and medical student associations, district health officers, hospital directors, regional traffic police commanders, and chairpersons of the motorcycle riders’ associations in the respective regions, as well as with the rural trauma networks of first responders. Priority will be made to present the preliminary findings at an international conference hosted in Uganda and at the annual world safety conference. Anonymized participant data sets from this trial will be archived on a publicly accessible permanent weblink that will be provided by the publishing journal within 12 months from the actual date of completion of the trial.

## Results

The trial was approved on August 27, 2019. The actual recruitment of the first patient participant began on September 01, 2019. The last follow-up was on August 27, 2023. Posttrial care, including linkage to clinical, social support, and referral services, is to be completed by November 27, 2023. Data analyses will be performed in Spring 2024, and the results are expected to be published in Autumn 2024.

## Discussion

### Study Implications and Future Directions

This trial is meant to compare (1) the time interval from the accident to hospital admission, (2) the time interval from the referral decision to hospital discharge, (3) the all-cause mortality, and (4) the morbidity of patients with motorcycle accident–related orthopedic and neurological injuries between RTTDC (intervention) and standard care (control) study centers in Uganda, Africa.

This study is anticipated to reveal the overall impact of the rural trauma team development and training on the clinical process time efficiency and patient-centered outcomes of musculoskeletal and neurological injuries in controlled clinical settings, using validated injury severity scores [43] and trauma outcome and process measures [29,30]. The findings will add value to the emerging evidence from previous nonrandomized studies in high-income countries, which have evaluated the RTTDC. The available evidence suggests that the RTTDC potentially reduces the prehospital interval [50] and referral decision time [50], and enhances trauma team role identity, but has no perceived impact on mortality reduction [51]. It remains unclear how these findings relate to LMICs whose trauma care systems are still in the infancy stage.

### Study Limitations

Despite the strengths of this trial, we anticipate some limitations. First, while the authors are ambitious to assume that the study centers are homogeneous, the heterogeneity among the 6 participating regional referral hospitals could cause bias and affect study estimates. Further, the relatively smaller number of clusters could affect the power of the study. However, randomization of 6 out of the 17 trauma centers is within the ethical constraints as this sample already represents 35.3% of Uganda’s regional referral hospitals. To overcome the statistical power bias limitation, the sample size is inflated for individual randomization to cater to the design effects in accordance with the report by Hooper et al [45]. Moreover, we plan to use mixed effects regression models, which permit adjustments for covariates at both the cluster and individual levels in a single-stage approach, and plan to use the *t* test, which is robust in terms of normality deviations. According to Borhan et al [52], mixed effects models are deemed suitable for smaller clusters in situations where the primary outcomes are continuous, which is the case in this trial. Further, we hope that the ancillary studies with mixed methods will add value to the overall interpretation of the trial results by providing data from individuals outside the health sector, such as traffic law enforcement professionals.

